## Abstract

**Background:**

The end of life for cancer patients is the ultimate stage of the disease, and care in this setting is important as it can improve the wellbeing not only of patients, but also the patients' family and close friends. As it is a matter of profoundly personal concerns, patients' perception of this phase of the disease is difficult to assess and has thus been insufficiently studied. Nonetheless, caregivers are required to provide specific care to help patients and to treat them in order to improve their wellbeing during this period.

While tools to assess health-related quality of life (QoL) in cancer patients at the end of life exist in English, to our knowledge, no validated tools are available in French.

**Methods/design:**

This randomized multicenter cohort study will be carried out to cross-culturally adapt and validate a French version of the English QUAL-E and the Missoula Vitas Quality Of Life Index (MVQOLI) questionnaires for advanced cancer patients in a palliative setting. A randomized clinical trial component in addition to a cohort study is implemented in order to test psychometric hypotheses: order effect and improvement of sensibility to change.

The validation procedure will ensure that the psychometric properties are maintained.

The main criterion to assess the reliability of the questionnaires will be reproducibility (test-retest method) using intraclass correlation coefficients. It will be necessary to include 372 patients. The sensitivity to change, discriminant capability as well as convergent validity will be also investigated.

**Discussion:**

If the cross-cultural validation of the MVQOLI and QUAL-E questionnaires for advanced cancer patients in a palliative setting have satisfactory psychometric properties, it will allow us to assess the specific dimensions of QoL at the end of life.

**Trial registration:**

Current Controlled Trials NCT01545921.

## Background

The end of life for cancer patients is the ultimate stage of the disease. However, in this setting, improving quality of life (QoL) and the wellbeing of patients should remain a major concern. Given the profoundly personal concerns involved, patients' perceptions of the end of life are difficult to assess and have therefore been insufficiently studied. Clinicians, nurses, and other paramedical personnel are required to provide individualized care adapted to the end of life in order to improve patients' QoL and wellbeing [1,2].

Today, there is no consensus to define the time frame related to the 'end of life' of a cancer patient [3]. For example, depending on the cancer site, the 'palliative' period could vary from a few days to a few months. Moreover, the palliative and 'end-of-life' periods could overlap, but the therapeutic goals for these two periods should not be the same. In order to provide optimal care, it seems crucial to distinguish between these two periods as the former has a more therapeutic goal while the latter is to accompany patients as they near death. This ultimate stage of disease could require caregivers to meet new demands not only from patients, but also from their relatives.

To our knowledge (Patient Reported Outcome and Quality Of Life Instruments Database) [4-6] there are no French validated tools to assess health-related QoL for cancer patients at the end of life. QoL is a major endpoint to assess therapeutic strategies in cancer patients, particularly in a palliative setting when no benefits in overall survival can be expected. In this context, QoL should be considered the primary endpoint for trials [7,8].

QoL at the end of life could be evaluated using generic QoL questionnaires like EORTC QLQ-C30 and/or the Medical Outcome study Short Form 36 (SF-36) or by using questionnaires focusing on symptoms. For example, the Edmonton Symptoms Assessment System (ESAS) is a dedicated tool to assess pain [9]. Other tools allow caregivers to assess depression [10] or fatigue [11].

Some studies have highlighted the fact that additional specific items could be required to take into account the most important QoL dimensions or symptoms at the end of life such as symptom and pain management [12-16], quality of care [15,16], preparation for death [12,13], relationships/communication [12-14], family context [16], dignity [12,16], choice and control [12] the financial aspect of care [17,18], completion [18], or spirituality/transcendence [14-16,18].

Current tools to assess QoL do not explore these specific dimensions, which could capture major aspects of QoL at the end of life.

Some questionnaires dedicated to the palliative setting have been proposed, but they are too long, and\or specific domains related to the end of life are not explored. Validated QoL tools in French are even more restricted; only the Mc Gill [19,20] Support Team Assessment Schedule (STAS) [21] and QLQ-C15 PAL questionnaires (shortened version of QLQ-C30) [22] are available. Moreover, these tools are more specifically dedicated to the palliative setting.

The Missoula-Vitas Quality Of Life Index developed by Byock *et al*. has been specifically designed for the end of palliative setting [14]. This QoL tool provides an exhaustive assessment of major dimensions in that setting. The shortened version included only 15 items investigating five dimensions: symptoms, function, interpersonal relationships, wellbeing, and transcendence [14]. Another tool, the QUAL-E, is longer and includes 25 items that investigate five domains: life completion, relations with the healthcare system, preparation for end of life, symptom severity, and affective social support [18]. However, these QoL tools have not been adapted to French culture and translated into French. Another concern is that they are not specific to cancer patients.

The first step to improve evaluations of how French patients perceive this disease setting is to translate the available specific 'end-of-life' QoL tools. Assessing QoL at the end of life with dedicated tools could help to compare therapeutic strategies and could improve care in the palliative setting. Based on these hypotheses, we propose to adapt QoL tools dedicated to the end of life to French culture and to validate them for French cancer patients.

## Methods

### Objectives

Primary objectives are: to cross-culturally adapt the English questionnaires QUAL-E and MVQOLI (Missoula Vitas Quality Of Life Index) and to validate their psychometric properties in the end-of-life setting.

Intermediate objectives are: to translate and adapt the English version of QUAL-E and MVQOLI into French taking into account cultural differences.

Secondary objectives are: to longitudinally assess QoL of cancer patients until death using the QLQ-C15 PAL, the French version of QUAL-E and the Missoula Vitas Quality of Life Index (MVQOLI); to assess the impact of therapeutic strategies on QoL at the end of life; to assess the added value of spontaneous completion of QoL questionnaires to detect a clinically significant change in this setting; to assess the effect of the order of questionnaires on QoL levels; to define a time period for the 'end of life'.

Primary outcomes for cross-cultural and psychometric validation (see also statistical methods): reproducibility of QoL scores estimated by intraclass correlation coefficients; sensitivity to change estimated by effect size and the standard error of mean; discriminant capability; and convergent validity.

### Study design

We propose to perform a prospective multicenter cohort study. A randomized clinical trial component in addition to a cohort study is implemented in order to test psychometric hypotheses related to order effect and to the improvement of sensibility to change. This study has been designed in accordance with the validation methods of the FDA and the International Society For Pharmacoeconomics and Outcomes. It was reviewed by a national patients' committee in July 2009. The Clinical trial was registered to the French Safety Agency for Health Products (AFSSAPS, that is the Health Authority in France). Although this study does not assess health products, it was registered as biomedical research. The authorization was in agreement with the Article L. 1123-8 Code of Public Health and was obtained in February 2010.

This clinical trial was registered at AFSSAPS (2010-A00196-33). The project was approved by the local ethics committee (CPP Ouest II Angers) in April 2010.

The Study was registered in March 2012 on ClinicalTrials.gov; the registration number is NCT01545921.

The project received a grant so-called PHRC (Programme Hospitalier de Recherche Clinique 2011) in 2011 from the French national cancer institute (INCa, Institut National du Cancer).

### Population

To be eligible, patients should have been diagnosed with advanced cancer (with any cancer site) and treated or not with palliative intent (chemotherapy, analgesic radiotherapy, surgery without curative intent), with an ECOG or a WHO performance status ≥ 2, a life expectancy ≥ 1 month, and an age ≥ 18 years.

Patients should have been informed about the palliative stage of the disease and should have been followed for at least 1 month by a palliative caregiver to be included in the study.

The non-eligibility criteria are: a psychiatric disease that compromises understanding of the study objectives and/or informed consent and/or the inability of patients to follow the study design for psychological, social, family, or geographical reasons.

Written informed consent is required before inclusion.

### Recruitment

Once eligibility criteria have been checked, patients from French comprehensive cancer care centers or hospitals will be invited to join the study.

Before inclusion, patients should read and understand the study information letter and then should date and sign the informed consent form (ICF) to allow them to join the study.

The coordinating center will be notified of each inclusion before completion of the first QoL questionnaire (inclusion document will be completed and returned to Paul Papin Center, Angers by fax).

Since eligibility criteria will be checked and patients' ICF will be collected, the first QoL questionnaires and the test-retest (3 days after the first completion) will be completed (before randomization) in the following order: QLQ-C15 PAL, MVQOLI, and QUAL-E.

After completion of the retest QoL questionnaire, the eligibility criteria and date of signed informed consent will be collected on a dedicated internet site to allow e-randomization with a personal log-in and password (Tenalea software). The study coordinator will then be able to randomize patients. The allocated arm will be sent to investigators, to the methodologists, the principal investigator and the coordinating center by email.

Patients will be randomized after the test-retest to limit the number of non-assessable patients for reproducibility.

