### Randomization

To explore secondary objectives 3 and 4 using a factorial design, QoL questionnaire order, and spontaneous QoL completion will be randomized 1:1:1:1 using a minimization technique stratified according to center, cancer location, sex, and age.

Patients will be randomized in one of the following four arms (Table 1): (1) Arm A: MVQOLI then QLQ-C15 PAUL and QUAL-E, evaluation every month; (2) Arm B: QLQ-C15 PAL, MVQOLI and QUAL-E, evaluation every month; (3) Arm C: MVQOLI then QLQ-C15 PAL and QUAL-E, evaluation every month and spontaneous QoL completion; and (4) Arm D: QLQ-C15 PAL, MVQOLI and QUAL-E evaluation every month and spontaneous QoL completion.

**Table 1 T1:** Follow-up for QoL and data collection according to randomized arms

	Baseline		Follow-up	
	**D1^a^**	**Between** **D1 and D3^b^**	**Before every consultation until death (J30+/-3 days)**	**If necessary according to randomized allocated arm (notebook)**

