**Collected data and order of administration for QoL questionnaires**				

	**Arms**	**Arms**	**Arms**	**Arms**

Consent	A/B/C/D			

Questionnaires: QLQ-C15, MVQOLI and QUAL-E	A/B/C/D	A/B/C/D	B and D	

Questionnaires: MVQOLI, QLQ-C15 and QUAL-E			A and C	

Questionnaires: MVQOLI, QLQ-C15				D and C

Performance Status, Performance Palliative Scale	A/B/C/D	A/B/C/D	A, B, C, D	

Vital signs, pain (EVA)	A/B/C/D	A/B/C/D	A, B, C, D	

Care (Oncology, Psychology, and so on)	A/B/C/D	A/B/C/D	A, B, C, D	

Responsiveness question	A/B/C/D	A/B/C/D		D and C

^a^D1: First day, the day where the first QoL questionnaires will be completed; D3: 3 days after the first day administration

^b^Can be done D1 at the end of the day if the first was done early in the day

^c^Only MVQOLI and QUAL-E

The above randomization was chosen to explore methodological aspects to optimize QOL tools in the end-of-life setting.

It will allow us to assess the occurrence of an order effect on QoL level by investigating a halo effect and/or a framing effect. Since every patient should complete three questionnaires (MVQOLI, QUAL-E, and the QLQ-C15 PAL), completion of the first questionnaire could influence responses for the following questionnaires, resulting in different QoL levels. Moreover, this effect could be differential depending on the completion order. Since QUAL-E needs a face to face interview, it will be completed by the patient at the end for each arm.

The second randomization will investigate the added value of spontaneous QoL completion to capture clinically important changes in QoL that could have occurred between two planned QoL assessments.

For each allocated group a specific case report form (CRF) will be produced with the corresponding order of QoL questionnaires to prevent changes in completion order (that is, 'cross-over') after the randomization.

Furthermore, the date and time of completion for each QoL questionnaire will be collected. This will allow us to check the order of completion used by the patients.

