#### Primary objective analyses

This study will respect the FDA psychometric validation methods [7].

The first objective is to validate translation of QUAL-E and MVQOLI by checking the psychometric properties.

1. Validity [32-34]: Face validity and content validity: The translated questionnaires will be analyzed by patients and experts to check that the items of the questionnaires are in line with to the original version (major domains treated, question ambiguity). This step was conducted by the '*Qualité de vie et cancer' *platform experts group during cross-cultural translation of the English questionnaires.

Criterion validity: We will check that the translated tools correlate with reference QoL or clinical criteria by calculating correlation coefficients. QLQ-C15 PAL will be treated as the gold standard for QoL tools. A strong correlation between the measures given by the questionnaires and those given by the QLQ-C15 PAL will constitute proof of criterion validity. We will also use the WHO performance status and the performance palliative scale (PPS). These variables will be also dichotomized to calculate the sensitivity and specificity of QoL tools using ROC curves.

Construct validity: This psychometric property will be checked by calculating establishing convergences and differences with the other variables. Factorial analyses as well as Item Response theory methods will be used.

2. Reliability [32-34]: Effect size and the standardized response mean will be computed between each follow-up and then analyzed according to Cohen's classification.

Sensitivity to change:

Internal consistency: we will estimate the strength of the inter-correlations between items, and validate underlying dimensions. We will calculate Cronbach's alpha as an estimator of this internal consistency for each dimension of the QoL questionnaires (at each time assessment). This estimator must be greater than 0.7 to consider a domain homogeneous, but not too close to 1, which would mean that some questions are redundant.

Reproducibility will be studied by calculating ICC using analysis of variance for repeated measurement. An ICC of 0.65 is the minimum required for reproducibility. A Bland and Altman graph will be also done [35,36].

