### Longitudinal analyses

QoL will be described at each follow-up and then longitudinally analyzed using a mixed model analysis of variance for repeated measurements to investigate and test a time trend for QoL [39-41]:

These models will have to take into account non-random missing data.

With simple imputation methods for sensitivity analyses:

Mean QoL score imputation: Means will be calculated for the whole population and for specific patient profiles (cancer location, age, sex, and so on) at each follow-up and then will be imputed for patients with missing QoL scores

Extreme QoL score imputation. This method could be used when the missing data are due to a pejorative event such as death or disease progression.

With 'pattern mixture' models [42,43]:

Qualitative variables will be created to describe missing QoL score profiles and to define patterns for these analyses (no missing score, intermittent and drop-out profiles).

Time until definitive QoL score deterioration:

Analyses of time until a definitive QoL score deterioration (TUDD) will be estimated using the Kaplan-Meier method [44].

The TUDD of a score will be defined as the time interval between randomization and the first decrease in the MCID score ≥ 5 points compared to the QoL score at inclusion with no further improvement in QoL score ≥ 5 points or in the case of patient who dropped out after a ≥ 5-point decrease, resulting in missing data.

Patients will be censored at the last QoL follow-up when no ≥ 5-point deterioration in the QoL score from baseline will be observed or for patients with a ≥ 5-point deterioration, but with a subsequent ≥ 5-point improvement as compared to baseline QoL score.

Patients with no available QoL scores will be included in the TUDD analysis, but censored immediately.

2. To assess the impact of therapeutic strategies on QoL at the end of life Since treatments and care strategies will be longitudinally collected, for exploratory purposes only, we will compare longitudinal QoL according to these strategies using mixed model analysis of variance and Log Rank tests and Cox models for the time to definitive QoL deterioration analyses.

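### Arms A and C change questionnaire order between baseline and follow-up, so their comparisons with inclusion mix true change with any order effect

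*Protocol article*

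**What the plan says.** **Baseline.** Under Recruitment, all patients complete D1 and the retest before randomization, and these "will be completed (before randomization) in the following order: QLQ-C15 PAL, MVQOLI, and QUAL-E". Table 1 agrees: all four arms stand in that row at both baseline columns.

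**Follow-up.** Under Randomization, two arms change the order: "Arm A: MVQOLI then QLQ-C15 PAUL and QUAL-E, evaluation every month" and "Arm C: MVQOLI then QLQ-C15 PAL and QUAL-E, evaluation every month and spontaneous QoL completion". The other two keep it: "Arm B: QLQ-C15 PAL, MVQOLI and QUAL-E, evaluation every month" and "Arm D: QLQ-C15 PAL, MVQOLI and QUAL-E evaluation every month and spontaneous QoL completion". QUAL-E is last in every arm.

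**Expected effect of order.** The text below Table 1 warns that "completion of the first questionnaire could influence responses for the following questionnaires, resulting in different QoL levels", and adds that the effect may differ by order.

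**Analyses that look back to baseline.** Under Longitudinal analyses, TUDD is a drop of at least 5 points "compared to the QoL score at inclusion", and a mixed model tests a time trend. Objective 5 (defining the end-of-life period) reuses both. For sensitivity to change, Primary objective analyses states: "Effect size and the standardized response mean will be computed between each follow-up". Order is analyzed under objective 4 only.

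**The concern.** A change score is interpretable when both measurements are taken under the same conditions. In B and D they are, at planned visits. In A and C the sequence of the first two forms changes once, exactly at the boundary between baseline and follow-up. If order matters as the protocol suspects, the step from baseline to month 1 in those arms contains a shift that is not a change in the patient's QoL. The shift would then persist at every later planned visit.

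Three results are exposed:
- **TUDD.** A lasting downward shift brings patients nearer the 5-point threshold and an upward shift hides real decline. Because the shift recurs at each planned visit, the requirement of no later improvement would not filter it out.
- **Time trend (objectives 1 and 5, and the time effect under objective 2).** With baseline in the model and no order term, part of the shift is read as time.
- **ES/SRM from baseline to month 1, if computed.** The shift could look like responsiveness or offset it.

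**Working it through.** The plan states no figure on this point, so the check sets the order by arm and period side by side and then illustrates the size.

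**1. Order by arm and period** (Recruitment, Randomization, Table 1)

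| Arms | D1 and retest | Planned follow-up | Same order? |
|---|---|---|---|
| A, C | QLQ-C15 PAL, MVQOLI, QUAL-E | MVQOLI, QLQ-C15 PAL, QUAL-E | No |
| B, D | QLQ-C15 PAL, MVQOLI, QUAL-E | QLQ-C15 PAL, MVQOLI, QUAL-E | Yes |

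Share that switches: 2/4 = 50%; 372 × 0.5 = 186 patients.

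**2. Which comparisons carry the shift.** Let Δ be the true mean change and d an additive order shift.
- Change from inclusion: Δ + d in A/C, Δ in B/D, and Δ + d/2 pooled.
- Change between two later planned visits: d cancels within each patient.
- Test-retest ICC: one order at both times, before randomization, so d is absent.
- A+C versus B+D at follow-up: the difference is d, which is what objective 4 estimates. The shared baseline does not bias it. No arm has MVQOLI first throughout, so it cannot separate MVQOLI first from order changed since baseline.
- A+B versus C+D: each side has one switched arm, so d cancels in mean differences at planned visits.
- QUAL-E: always third. Only the sequence of the two forms before it changes.

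**3. Illustration.** Neither d nor the SD of change s is in the document. I assume d of 2 to 5 points, s of 15 to 25, and no true change, on a 0–100 score. The article gives that range for the QLQ-C15 PAL; MVQOLI is scored differently.
- Pooled mean bias = d/2: 1.0 to 2.5 points.
- SRM shift in A/C = d/s: from 2/25 = 0.08 to 5/15 = 0.33.
- SRM shift pooled = (d/2)/√(s² + d²/4): 0.04 to 0.16.
- Share of A/C patients at least 5 points below inclusion at a single visit = Φ((−5 − d)/s), with d signed:

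| s | d = 0 | d = −2 | d = −5 | d = +2 | d = +5 |
|---|---|---|---|---|---|
| 15 | 36.9% | 42.1% | 50.0% | 32.0% | 25.2% |
| 20 | 40.1% | 44.0% | 50.0% | 36.3% | 30.9% |
| 25 | 42.1% | 45.2% | 50.0% | 39.0% | 34.5% |

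These are single-visit crossings, not TUDD rates.

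**4. Could a null objective 4 result clear the other analyses?** Take a two-sided 5% comparison of mean change at one visit, 186 versus 186, with no attrition: power ≈ Φ(d/(s√(2/186)) − 1.96).
- d = 5: 0.90, 0.67, 0.49 for s = 15, 20, 25.
- d = 2: 0.25, 0.16, 0.12.

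A non-significant result would not exclude a shift of a few points. A repeated-measures analysis may differ from this one-visit figure.

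**5. After the fix.** With an indicator equal to 1 in A/C after baseline and 0 otherwise, a constant additive shift goes to that coefficient and the time effect estimates Δ. The pooled bias falls from d/2 to 0. No sample size changes.

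**The case against.** The strongest reply is that covariates in a mixed model are matters for the SAP, which the article says will be written before database lock, and that the article never states that arms are pooled without regard to order. Objective 4 already compares trajectories and TUDD by order, and arm-specific CRFs with recorded completion times mean that the order of each form can be checked. The common baseline is also deliberate: randomizing after the retest limits the number of patients not assessable for reproducibility.

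Much of this stands. The common baseline needs no change, and objective 4 supplies most of the machinery. But the switch itself is a design feature that the article fixes, and it names order as a likely source of different scores. Objective 4 is a between-group comparison. It does not carry order into objectives 1, 2 and 5 or into sensitivity to change.

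The objection is right on reach. A reader might infer that the primary validation as a whole is compromised because sensitivity to change is listed among the primary outcomes. The document does not support that. The sample size rests on the ICC, which is untouched. ES and SRM are described as between follow-ups, so at most the first interval is involved, and only in A and C. A reader might also take the illustrated percentages as expected false deteriorations. They are single-visit figures under assumed values, and TUDD also depends on later scores.

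**Conclusion.** The concern holds in limited form. In half the patients, comparisons with inclusion (TUDD, the overall time trend, and baseline-to-month-1 ES/SRM if computed) confound true change with any order effect. The primary ICC, the randomized mean contrasts and changes between later planned visits are not affected. For QUAL-E only the sequence of the preceding forms differs.

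The size is unknown and is zero if order has no effect. Under the assumed shifts and SDs, the pooled mean bias is 1.0 to 2.5 points and the pooled SRM artefact is 0.04 to 0.16. Within A/C alone the SRM artefact is 0.08 to 0.33. This does not invalidate the design, but it should be settled in the analysis plan before lock.

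**What to change.** Leave visits, randomization and sample size as they are. In the analysis plan:
1. In the mixed models for objectives 1, 2 and 5, add a post-baseline order indicator (A/C versus B/D, set to zero at D1 and retest).
2. Report baseline-to-month-1 ES/SRM, if computed, by order group. Report TUDD by order group, or stratify it by order. ES/SRM between later planned visits may stay pooled.
3. Add a sensitivity analysis in B and D, using planned visits only.
4. State that the order term is kept whatever the objective 4 test shows.
5. Reconcile the order in the spontaneous booklet. Table 1 lists MVQOLI then QLQ-C15 for both C and D, while the section on completion of the questionnaires names QLQ-C15 PAL first. If Table 1 applies, arm D also changes order on spontaneous forms. This must be settled before those forms enter the TUDD sensitivity analysis.

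The cost is one model term and wider intervals for order-specific estimates. With 186 instead of 372 patients and the same SD, the standard error is √(372/186) = 1.41 times as large.
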